## Analysis

### Outcomes

#### Primary objectives

The primary objective of this study will be to assess the clinical effectiveness of CirrhoCare’s digital therapeutic management system.

#### Primary endpoints

The primary endpoint of this study will determine whether, following hospital discharge after an acute decompensation admission, the CirrhoCare management system leads to a reduction in unplanned medical interventions for new-liver related complications, within 90 days from hospital discharge. Planned interventions are defined as scheduled appointments as part of the patient’s standard of care, or any intervention initiated by a liver specialist (consultant, specialist trainee or prescribing nurse practitioner). This includes but is not limited to scheduled admissions, clinic appointments, day-case procedures and interventions and actions facilitated by the CirrhoCare system. All other medical interventions should be considered unplanned.

New liver-related complications are defined as:

Overt encephalopathy (defined by a grade ≥2 according to the West Haven criteria).^17^Dehydration (defined by either AKI criteria according to the International Club of Ascites)^18^:Creatinine greater than 1.5 times baseline.Creatinine increase >0.3 mg/dL or >26.5 umol/L within 24–48 hours.Increasing ascites (defined as large volume grade 3 ascites).Variceal bleeding.Infection—defined by the following:Presence of positive cultures from urine, ascites, sputum or blood, or radiological chest criteria, or SBP with polymorphonuclear counts >250 cells/mm^3^.High clinical suspicion of infection warranting inpatient, pre-emptive antimicrobial treatment.

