**Methods and analysis:**

CirrhoCare is a prospective, multicentre, randomised controlled trial comparing the CirrhoCare management system with standard-of-care for high-risk cirrhosis patients who have been discharged following an admission with acute decompensation. The CirrhoCare management system comprises a novel digital platform for use in a patient’s home, designed to proactively detect the first signs of new decompensation in patients with established cirrhosis, discharged to the community. This enables a clinician to instigate early community-based care or, if needed, to triage the patient for hospital interventions.

214 patients will be recruited to the CirrhoCare trial from at least 12 UK centres. Patients will be randomised on a 1:1 ratio allocation to the CirrhoCare Management System or standard of care. Participants who are randomised to CirrhoCare will receive a CirrhoCare health kit comprising a smart watch, smart phone with enabled SIM (Subscriber Identity Module) network card, blood pressure monitor, weighing scales and thermometer. Participants will take measurements every morning Monday to Friday and will be followed up for 90 days postdischarge.

The primary objective of this study is to assess the clinical effectiveness of the CirrhoCare digital management system. We hypothesise that its early community-based intervention will reduce the number of unplanned hospital interventions and admissions and prevent liver-related complications when compared with standard-of-care management.

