Studies have shown that specialist follow-up after discharge is associated with a lower 30-day readmission rate and 12-month mortality.^13^ However, the current standard of care following discharge from hospital for an acute decompensating event is reactive, and significant regional variations exist within our current liver care pathways, leading to regional inequalities, highlighted by the UK Liver Atlas 2017 report.^14^ Patients also often present to hospital late with significant liver-related complications, due to the inadequacies of current care pathways in enabling advanced warning of changes to clinical status in the community. A patient and public involvement (PPI) workshop study preceding our Pilot study highlighted that carers feel poorly supported and are unsure from whom to seek help if a decompensating event occurs. This is in addition to overstretched primary care which struggles to cope with such complex patients. Attempts have been made to identify readmission prediction markers in order to create risk stratification models, but with little success to date.

The CirrhoCare management system (figure 1) is a novel, patient-centred, home digital therapeutic approach created to address some of these issues. It aims to allow regular patient monitoring via the automatic upload of patients’ physiological measurements, along with daily weights and assessment of hepatic encephalopathy, to a clinician facing digital dashboard with an inbuilt text messaging service. This allows two-way communication between the patient and clinician. The clinician may also choose to speak to the patient via regular telephone calls if required. CirrhoCare aims to identify the early signs of an acute decompensating event, thereby allowing proactive community-based management and prioritisation of early assessment if required, avoiding emergency hospital interventions including use of costly resources.

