### Completing measurements

If randomised to the intervention arm, ideally prior to hospital discharge, or within 14 days of discharge, patients will be trained on a CirrhoCare healthcare kit so that they are able to complete their assessments at home. The participants will then be expected to complete their assessments every morning, Monday to Friday. The average time taken to complete a full assessment is 12–15 min. These data will then be analysed by the CirrhoCare clinical research team who will, when required, provide patients with clinical advice including to repeat measurements, to alter medications, to attend an urgent clinical review or the accident and emergency department, either via the text messaging function on the app or by direct clinical contact. In the evening, the patient will complete the medication and dietary/fluid intake log on the CirrhoCare app.

If a participant fails to input their measurements, the research team may send a reminder via the app, or instigate further contact under their discretion, if indicated. If the patient has not completed their measurements for three consecutive days, then the participant will be contacted by a member of the trial team.

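### The primary endpoint excludes CirrhoCare-facilitated actions as planned, an exclusion open to one arm only, so the wording lets like emergencies be counted differently by arm

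*Protocol article*

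**What the plan says.** The Primary endpoints section asks whether the system "leads to a reduction in unplanned medical interventions for new-liver related complications, within 90 days from hospital discharge". An intervention counts only if it is unplanned. Planned care covers scheduled appointments and "any intervention initiated by a liver specialist (consultant, specialist trainee or prescribing nurse practitioner"). A non-exhaustive list of examples follows, ending with "day-case procedures and interventions and actions facilitated by the CirrhoCare system. All other medical interventions should be considered unplanned".

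Two other places show what the system may set in motion. Under Completing measurements, the research team may advise an intervention-arm participant "to alter medications, to attend an urgent clinical review or the accident and emergency department". The abstract (Methods and analysis) says: "This enables a clinician to instigate early community-based care or, if needed, to triage the patient for hospital interventions".

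Of usual care, the Introduction says that "the current standard of care following discharge from hospital for an acute decompensating event is reactive". Study design describes the trial as unblinded. Monitoring provides for a clinical adjudication committee that audits clinical interactions.

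**The concern.** Whether a complication enters the primary endpoint should not depend on something only one arm can have. Here it can. Suppose two patients develop the same listed complication and reach the same emergency department. One was told to go by the CirrhoCare team and the other went unprompted. The wording allows the first to be a non-event and makes the second an event, unless it was scheduled or a liver specialist initiated it.

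The liver-specialist clause applies to both arms, but it makes classification turn on who acted rather than on what happened to the patient. It may also apply unequally, since usual care is described as reactive while the intervention arm has a monitoring team that can act.

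At stake is what a positive result would mean. The abstract hypothesises fewer unplanned interventions and admissions, and prevention of liver-related complications. An attendance left out because the system prompted it is neither a prevented complication nor an avoided attendance.

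**Working it through.** **Inputs from the Sample size section.** Event rates 35% (CirrhoCare) and 60% (standard of care); Fisher-Irwin exact test; two-sided 5%; 90% power; 15% loss; 182 evaluable (91 per arm); 214 randomised.

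**Reproducing the plan's figure.** Full enumeration of the two-sided Fisher test at 91 per arm, 35% vs 60%, gives power of 89.8% against the stated 90%. The continuity-corrected formula gives 90 per arm. Inflation: 182 / (1 − 0.15) = 214.1, against 214. The sample-size arithmetic is sound; the problem lies in the endpoint rule.

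**Assumptions.** The article gives neither share below, so both are varied. A binary outcome per patient is inferred from the sample-size test.
- f: share of intervention-arm patients with an event who drop out of the count because their qualifying care is classed as planned.
- g: the same share in the control arm, where only scheduling or the liver-specialist clause can apply.
- No true effect: the true rate is 60% in both arms.

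**Formulas.** Observed intervention rate = 0.60 × (1 − f). Observed control rate = 0.60 × (1 − g). The probability of a significant benefit is the sum, over all outcome pairs with Fisher p ≤ 0.05 and fewer events on CirrhoCare, of the product of the two binomial probabilities (n = 91 each).

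| f | g | Observed rates (CirrhoCare vs control) | P(significant benefit) |
|---|---|---|---|
| 0 | 0 | 60% vs 60% | 1.8% |
| 10% | 0 | 54% vs 60% | 9.5% |
| 20% | 0 | 48% vs 60% | 30% |
| 41.7% | 0 | 35% vs 60% | 90% |
| 20% | 10% | 48% vs 54% | 9.0% |
| 30% | 10% | 42% vs 54% | 30% |
| 41.7% | 20% | 35% vs 48% | 37% |
| 20% | 20% | 48% vs 48% | 1.6% |
| 10% | 20% | 54% vs 48% | 0.15% |

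The 41.7% value is (60 − 35) / 60, the share at which relabelling alone would create the whole planned contrast when g = 0. It is a reference point, not an estimate of what will happen.

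With a true rate of 53% (the 90-day readmission figure in the Introduction) and g = 0, the probability is 24% at f = 20% and 51% at f = 30%.

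The result is driven by the gap between f and g. Equal shares bring the probability back to about its nominal level. Nothing in the rule makes the shares equal.

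**The case against.** The strongest reply is that turning emergencies into earlier, arranged care is what the system is for, so a planned/unplanned endpoint is partly deliberate. That stands for arranged day-case or elective care, and the fix should respect it. It does not cover an emergency attendance that happens anyway and differs only in who suggested it.

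Two safeguards might be cited. The adjudication committee does not help, because a committee applying this rule correctly would reproduce the difference. Readmissions, length of stay and mortality are listed without restriction to unplanned care and would give a partial check, but they are secondary.

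A reader might also infer stronger claims that the article does not support:
- **That the same event under usual care is always unplanned.** The liver-specialist clause makes some control events planned too.
- **That every CirrhoCare-prompted emergency attendance must be excluded.** The text does not say whether care given by non-specialists after such a prompt is itself facilitated by the system. The wording permits the exclusion; it does not plainly require it.
- **That the bias always favours CirrhoCare.** This is true of the CirrhoCare clause taken alone. The specialist clause has no stated direction, and if g exceeded f the bias would run the other way (last row of the table).
- **That a liver team is in contact with intervention patients every weekday.** Patients measure Monday to Friday. The research team advises when required, and its make-up is not given in Completing measurements.

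**Conclusion.** The point holds as a defect in the wording of the primary endpoint. One exclusion is available to the intervention arm only, it can reach emergency and hospital care, and the companion exclusion depends on who initiated the care. The amount of bias cannot be predicted from the article, because f and g are unknown. Under no true effect, a 60% true rate, 91 per arm and a binary per-patient analysis, a gap of 10 percentage points between the shares raises the chance of a significant benefit from 1.8% to about 9%, and a gap of 20 points raises it to about 30%. These figures show sensitivity and are not a forecast. They are large enough that the rule should be changed before the primary analysis.

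**What to change.** Make the primary endpoint arm-neutral:
- Count every emergency attendance, non-elective admission or non-elective hospital procedure for a listed complication, regardless of who initiated or prompted it.
- For such events, remove both the CirrhoCare-facilitated and the specialist-initiated exclusions.
- Treat remote advice, community medication changes and pre-arranged elective or day-case care as non-events in both arms.
- Keep the current definition as a secondary outcome.

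The change should be made and documented before any arm-level results are seen. The article plans no interim analysis and expects recruitment to run to June 2026, subject to an extension.

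Costs: the protocol and analysis plan wording must be amended. Recruitment began in December 2023, so events already recorded would need reclassifying; the article does not show whether the recorded data are detailed enough for this. Redefining a primary endpoint in an unblinded trial under way needs a clear written justification. The observed effect may be smaller than under the present rule, and the 35% vs 60% assumption, and with it the power, may need restating.

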#### Secondary objectives

The secondary objectives of the study will be to assess the effect that CirrhoCare has on the individual components of the primary outcome over the 90-day follow-up period, including effect on severity of liver disease (using liver disease severity scores CLIF-C AD or MELD); effect on length of hospital stay (including intensive care admission), hospital readmissions and liver-related and overall mortality. The study will also aim to assess qualitative measures such as user experience, effects on quality of life (EQ-5D-5L) and frailty assessment (LFI).

Crucially, while the main objective is to determine the clinical effectiveness of the CirrhoCare programme, a formal cost-effectiveness analysis will be conducted to determine differences in healthcare costs between CirrhoCare and standard-of-care arms. Furthermore, a full work package of qualitative research will be undertaken, using questionnaires and interviews to identify barriers to implementing CirrhoCare in real-world clinical practice.

#### Data collection and storage

Trial data will be stored in a database created specifically for the CirrhoCare trial hosted by OpenClinica. Data entered into the CirrhoCare’s application will be stored in a secured NHS and General Data Protection Regulation compliant, Amazon Web Services cloud server, based in the UK. The UCL sponsor and CyberLiver will be responsible for data handling, storing, and processing of participant data collected via the app. The UCL sponsor and CyberLiver will follow the principles of the UK DPA.

#### Ethics and dissemination

The study has UK Research Ethics Committee (Health and Care Research Wales Committee) and Health Research Authority approvals. The information pack will be submitted locally to each NHS Trust’s Research and Development office by UCL CCTU. The results of this study will be published in peer-reviewed journals, disseminated at international conferences as well as established PPIE networks. The study has ISRCTN registration (ISRCTN11380842).

## Discussion

CirrhoCare aims to address the care gap that exists through remote digital monitoring and management of cirrhosis, using actionable insights to help diagnose complications early, allowing CirrhoCare to provide timely, cost-effective, community interventions. This also enables specialist liver care in remote geographical locations for integrated care delivery, with additional environmental benefits through fewer hospital journeys. This aligns well with the NHS long-term vision to improve outcomes in chronic conditions, like cirrhosis, through digitally enabled, community-based care.^19^ Furthermore, it enables the delivery of sustainable hepatology care in what is already an overstretched and overburdened healthcare system.

This study also fits within the remit of the National Institute for Health and Care Research Invention for Innovation i4i Challenge programme,^20^ seeking to provide clinical effectiveness data for a new, cost-effective care pathway for cirrhosis, which can be rapidly implemented, given the strides already made in CirrhoCare’s product development and regulatory approvals.

This trial will assess the impact of CirrhoCare, a novel digital therapeutic management system, on the prevention of hospital intervention and readmissions, and the development of new liver-related complications in cirrhosis patients. Furthermore, the study extends to ancillary studies including a nutritional impact analysis and a planned assessment of all the digital biomarkers, to determine if there are correlations with pathophysiology and outcomes, which enable derivation of a new cirrhosis complications prediction tool.

We believe the robust, multifaceted study design, with clinical effectiveness, cost-effectiveness and qualitative arms, will provide valuable insights into the role of digital healthcare in advanced liver disease.
